## Abstract

**Background:**

Anxiety, conduct and depressive disorders represent three highly prevalent psychiatric conditions in adolescents. A shared underpinning of these disorders is a shortcoming in emotion regulation, connected to the functioning of the ventromedial prefrontal cortex. Thus, an intervention able to target the suggested neural correlate seems to be highly desirable, aiming to hinder a maladaptive development of emotion regulation abilities and chronification of associated psychiatric disorders. As transcranial direct current stimulation (tDCS) was repeatedly demonstrated as a safe and non-invasive method to modulate specific brain activity, research is in demand to evaluate neurotherapeutic applications in adolescents with psychiatric disorders.

**Method:**

This transdiagnostic, randomized, triple-blind and sham-controlled clinical neurostimulation trial primary aims to investigate if emotion regulation abilities are increased after tDCS in adolescents with psychiatric disorders. Secondly, disorder-specific changes in the anxiety, depression or conduct disorder will be investigated, as well as changes in quality of life, and cognitive and emotional functioning after tDCS intervention. We will include 108 adolescents with psychiatric disorders, displaying a substantial deficit in emotion regulation. Of these, one third each has to be primarily diagnosed with a depressive, anxiety or conduct disorder, respectively. Participants will be randomized to the experimental group (*n* = 54) receiving real anodal tDCS, or to the control group (*n* = 54) receiving sham tDCS. Brain stimulation will be applied for 20 min on five consecutive days twice targeting the ventromedial prefrontal cortex (vmPFC). Changes in emotion regulation, together with changes in disorder-specific clinical symptoms will be recorded by multi-informant psychological ratings. To inspect changes in behavior and gaze, computerized tasks and an eye tracker system will be used. Changes in brain responses to emotional and cognitive stimuli will be examined with three functional magnetic resonance imaging (fMRI) paradigms. In addition, a resting state MRI will be acquired to investigate possible changes in brain connectivity.

**Discussion:**

By investigating “emotion regulation” as transdiagnostic treatment target, this project is oriented toward the Research Domain Criteria framework with a dimensional view on mental illness. The study aims at investigating the potential of tDCS as non-invasive intervention for depressive, anxiety and conduct disorders in adolescents and broadening the scientific foundation for its clinical application.

**Clinical Trial Registration:**

The study is ongoing and has been registered in the German Registry of Clinical Trials (DRKS-ID: DRKS00025601X) on the 28.06.2021.

## Introduction

### Psychiatric Disorders and Emotion Regulation

Given the high prevalence of mental health disorders in children and adolescents with its related psychological strain and suffering, parallel to the still limited efficacy of treatment options, there is a necessity to develop suitable, interventional approaches to support this vulnerable population. Estimates of prevalence of mental health problems before adulthood are generally broad and uneven due to methodological inconsistencies, with values currently ranging from 1 to 51% and a general pooled estimate of around 13.4% (1). In children and adolescents, three groups of mental disorders outstand in their numbers: anxiety (1st), conduct (2nd) and depressive disorders (4th) (1). In Austria, a recent epidemiological study indicated a point prevalence of psychiatric conditions in adolescents of 23.98% (±4.2), where anxiety disorders were most common (9.5%), and depressive (6.1%) and conduct disorders (3.7%) also presented significant amounts (2). The common presentation of anxiety disorders encompasses excessive fear and worrying that hinders global behavioral and social functioning (3), generally afflicting more females than males (4). Depressive disorders are characterized by symptoms such as frequent negative mood, anhedonia and loss of energy, self-deprecating and death thoughts, as well as psychomotor, sleep and appetite disturbances (5), again with a clear female preponderance. Contrary, conduct behavior disorders are more common in male adolescents, displaying diverse forms of externalizing aggression (e.g., fighting, bullying), destructive behavior (e.g., vandalism) and a general violation of rules (6). These three groups of disorders usually result in a heavy public health burden, often remain untreated, and commonly progress further into adulthood (7). Considering this developmental perspective, the importance to intervene as early as possible to hinder a further worsening of the symptoms and the chronification of the disorders into adulthood is obvious.

Conventional treatment approaches branch into two directions: firstly, pharmacological therapies, which are often accompanied by adverse effects, low compliance and off-label-use. Secondly, psychosocial and psychotherapeutical interventions (e.g., cognitive behavioral therapy), which often imply organizational challenges, such as long waiting lists or long treatment durations with related high costs (8).

Converging research in the last years showed that maladaptive emotion regulation is key to development and maintenance of psychopathological conditions, such as depression or anxiety disorder (9, 10). Examples of negative emotion regulation strategies are found across psychopathological states, as rumination in depression, deficit behavioral impulse control in conduct disorders or disengagement bias in anxiety (11). In contrast, successful emotion regulation was shown to act as a significant predictor of academic success/productivity in the classroom [total *R*^2^ = 0.29, *R*^2^ change = 0.07, F_(2, 204)_ change = 20.64, *p* < 0.001, β = 0.27] even after controlling for IQ (12), and was found to be positively related to ambition (*r* = 0.34; *p* < 0.001), to protean career orientation (*r* = 0.26; *p* < 0.001), and to perceived employability (*r* = 0.18; *p* < 0.01) (13), as well as to perceived workplace social support as predictor of job satisfaction and happiness (14).

Psychotherapeutic interventions already demonstrated the feasibility of improving emotion regulation and additionally reducing symptoms of the specific disorder (15). Underlying several psychiatric conditions, emotion dysregulation is a strong candidate for a transdiagnostic construct, and therefore, as a transdiagnostic treatment target (15).

### Neural Basis of Emotion (Dys-) Regulation—The Role of the vmPFC

The central role of the ventromedial prefrontal cortex (vmPFC) in emotion regulation is not only highlighted by its rich connections to cingulate cortex and subcortical structures like the amygdala (16). The vmPFC is shown to regulate the expression of fear responses [e.g., (17)], as well as the volitional suppression of negative emotion [e.g., (18)] by inhibiting amygdala activity i.e., subcortical down-regulation. Furthermore, the vmPFC is involved in critical psychological functions, such as in value-based decision making and social cognition, both highly relevant for modeling behavior depending on emotions (19).

Reduced functioning of the vmPFC, such as in neurological patients with focal vmPFC lesions, is generally linked to diminished emotional responsivity (20), problems to learn about rewards and punishment (21), impaired facial emotion recognition (22), reduced visual attention (23) and to generally reduced social emotions often linked to deficits in empathy, morality and theory of mind (20, 24, 25). In the same vein, aberrant activity in the vmPFC was repeatedly reported in diverse psychiatric disorders, such as in depression and anxiety (26), as well as in conduct disorder in adolescents (27), which further supports the vmPFC as an important common neurophysiological basis for emotion dysregulation in these disorders.

Considering the described domains of psychological (dys)functioning, their role for modeling behavior and their shared neurophysiological basis across the different disorders (19, 28), it is surprising that research regarding suitable neurobiological treatment approaches targeting the vmPFC is still in its infancy.

### Transcranial Direct Current Stimulation and Its Application in Psychiatric Disorders

Transcranial direct current stimulation (tDCS) is a non-invasive brain stimulation technique that uses low intensity currents (~1–4 mA) to reduce or enhance neuronal activity (29) by generating electric fields (30). In tDCS, the current flux is unidirectional and passed by a pair or set of electrodes with a determined electrode polarity, the so-called anodal or cathodal tDCS. This current direction is thought to induce polarity-dependent effects on neuronal excitability, being highly dependent on the network state of the target area (31). Concluding from stimulation of the primary motor cortex and its after-effects, reflected by the amplitude changes of motor evoked potentials, anodal tDCS increases and cathodal tDCS decreases cortical excitability (31). tDCS is also able to alter brain connectivity and thus likely modulate neural communication (32). Studies using resting-state functional magnetic resonance imaging (fMRI) demonstrated the ability of tDCS to alter functional connectivity of the motor and pre-frontal cortex, fronto-parietal and default-mode network (33, 34). Moreover, direct currents were demonstrated to influence ongoing oscillatory activity in several canonical electroencephalographic (EEG) bands such as theta, alpha, beta and gamma (35, 36). Thus, tDCS was reported to lead to acute changes in brain activity, as the neuromodulatory effects begin within seconds after the stimulation starts. On the other hand, physiological aftereffects of tDCS can last for several hours and days (37, 38) and repeated tDCS sessions can even lead to long-term effects via cumulative neuroplastic changes (39).

In the treatment of psychiatric disorders, several brain stimulation techniques are used. More invasive techniques such as electroconvulsive therapy (ECT) are highly effective for severe major depression disorder, but require a sedation of the participant and often have persistent side effects such as cognitive impairment (40). Transcranial magnetic stimulation (TMS), which induces electric current by an electromagnetic field, is less invasive and commonly used in the treatment of depression; side effects are milder but comprise the risk of seizures (40, 41).

tDCS, a stimulation technique known for its only transient and minor side-effects (39), was already tested in several clinical randomized-controlled trials in adult patient with different mental disorders, proving itself as a promising treatment and rehabilitation tool (42). Contrary to basic research investigating the effects of single-session stimulation [e.g., (43)] on general functioning, previous studies using repeated measurements over time showing cumulative neuroplastic benefits of repeated-session tDCS, with mostly 5–10 stimulation session (39).

In depressive disorders, where the left dorsolateral pre-frontal cortex is the most common target for anodal tDCS, a clinical trial showed the superiority of real tDCS over sham stimulation in 60 treatment-resistant patients (44). Several reviews and meta-analyses of randomized clinical trials have now established the safety and acceptability (45), as well as the effectiveness of tDCS compared to sham in alleviating depressive symptoms (42, 46). Most brain stimulation approaches for anxiety disorders used either high or low-frequency repetitive transcranial magnetic stimulation (rTMS) to target the prefrontal cortex (47). Up to date, only one randomized-controlled trial in adults with anxiety disorders was published, where a 5-sessions anodal tDCS treatment targeting the left pre-frontal cortex was not beneficial compared to sham stimulation to reduce anxiety symptoms (48). In a trial including 60 patients with opium use disorder, pre-frontal anodal tDCS combined with methadone was successful in reducing anxiety symptom when compared to sham with methadone and a methadone-only group (49). Up to date, only one tDCS trial in adults with conduct disorders was published and reported reductions in reactive aggression in an aggression task, as well as in self-reported aggression in a forensic population (50).

Encouraging results from studies in adults with psychiatric disorders are driving research into non-invasive brain stimulation (NIBS), particularly TMS and tDCS, in children and adolescents (51). Reviews report feasibility and promising efficacy of these stimulation techniques in various neurologic and psychiatric disorders in children and adolescents such as ASD, ADHD, epilepsy, depression, dyslexia, cerebral palsy and Tourette syndrome (51–53). TDCS proofed to be safe and well-tolerated in this age group. However, up to 2021, no studies with anxiety or conduct disorders were reported in the tDCS adolescent literature.

As a pediatric population might have accelerated neural plasticity after brain stimulation (54), an even greater effect on plasticity after NIBS is expected in children and adolescents. However, regarding the effects and possible side effects on the developing brain, extreme carefulness is warranted when treating this population. Moreover, the immature brain has to be considered as a unique physiological entity, as results from translational studies are missing (52, 55, 56).

Besides the reported literature gap regarding tDCS studies in adolescents with depressive, anxiety or conduct disorders, limitations of previous clinical tDCS studies included missing control groups, insufficient stratification and randomization, the exclusion of female patients, small sample sizes or only unimodal outcome measures (i.e., no psychophysiological or behavioral measures, but solely clinical disorder-specific self-reports) (53, 57, 58).

In line with the framework of the Research Domain Criteria project (RDoC of the United States' National Institute of Mental Health), which orients psychiatric research to uncover the neural systems underlying psychopathology and the behavioral components that flow across diagnostic categories (59), we will investigate the application of tDCS primarily targeting changes in emotion regulation abilities in children and adolescent with psychiatric disorders in general (transdiagnostic approach) as well as separately in each clinical disorder group (i.e., depressive, anxiety and conduct disorder subgroup). As secondary objective, we complementarily aim to investigate possible changes in disorder-specific clinical symptomatology (traditional, nosological approach; i.e., changes in the psychopathology of anxiety, depressive and conduct disorder). Thirdly, we will explore changes in quality of life, as well as in emotional and cognitive functioning in general.

Besides our perquisite for a treatment approach to be safe, non-invasive and free of major side effects, tDCS seems to be also advantageous on a neuroscientific level, because of its neuromodulative character, enabling changes in neural activity in specifically defined target regions. In that sense, a suitable stimulation target for our objectives needs to fulfill two requirements: Firstly, the brain region should play a central role in emotion regulation, integrating emotional and executive functioning (mirrored by strong connections to related brain areas). Secondly, the stimulation target, as a marker for deficient emotion regulation, should subsequently have been reported to be affected in the mentioned clinical populations. Both requirements were fulfilled by one brain region, namely the vmPFC. The vmPFC has not only been shown to be crucial for emotion processing (19), moreover several studies point toward wider regulation capabilities of the vmPFC (60–62), as a center for affective control, integrating emotional and executive functioning (63). Moreover, the vmPFC was reported to be—amongst others—dysfunctional in depression and anxiety (26, 63–65), as well as in conduct disorder in adolescents (27). Based on these theoretical requirements and the first positive investigations using conventional tDCS to target the vmPFC (60, 66–71), the vmPFC arises as an ideal brain stimulation region for the planned intervention which will include an optimized stimulation technique providing even higher focality, namely: HD-TDCS (50, 72).

## Methods and Analysis

The present clinical, interventional trial is designed as a randomized, triple-blind and sham-controlled study. The study protocol has been developed in accordance with the Declaration of Helsinki, approved by the review board of the Medical University of Vienna and registered in the German Registry of Clinical Trials (DRKS-ID: DRKS00025601X).

### Hypotheses

#### Primary Hypothesis

We expect that the participants of the experimental group (in total i.e., transdiagnostic, as well as in each clinical subgroup) will significantly improve in emotion regulation after real tDCS, when compared to the control group (in total i.e., transdiagnostic, as well as in each clinical subgroup) after receiving sham stimulation.

#### Secondary Hypotheses

We expect significant improvements in disorder-specific clinical symptomatology, quality of life, as well as in emotion recognition and regulation, attentional bias and working memory (in the related psychological, behavioral and physiological indices) in the experimental group, compared to the control group after the interventions.

### Participants

A total of 108 participants (*N* = 108) is planned to be recruited primarily from the Department of Child- and Adolescent Psychiatry (Medical University of Vienna, Austria) and private practices via information flyer and verbal study information. Psychological and behavioral pre- post measures, as well as the intervention will be carried out at the same institution. All MRI measures will be conducted at the High-Field MR Centre of the Medical University of Vienna in collaboration with the Department of Psychiatry and Psychotherapy.

#### Sample Size Calculations

Given the planned study design with two treatment conditions (real and sham tDCS), two time points (before and after the intervention) and three diagnostic groups (anxiety, depressive and conduct disorder), a repeated-measures analysis of variance (rmANOVA) with the following parameters was set up: α = 0.0167 (0.05 corrected for three groups), power 1 – β = 0.80, a moderate effect size of f = 0.25 (73). The FEEL-KJ [German version of the Questionnaire for the assessment of emotion regulation in children and adolescents; (74)] as it is used for assessment of the primary endpoint was reported to have a test-retest reliability of r = 0.62, a Chronbach alpha of α = 0.93 for the adaptive strategy subscale and a Chronbach alpha of α = 0.82 for the maladaptive strategies, whereas for the 15 different emotion specific subscales Chronbach alphas between α = 0.69 – α = 0.91 were reported (74). Non-sphericity is of no relevance for only two repeated measures. This, results in a required sample size of 36 per group and 108 subjects overall.

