#### Stratification and Randomization

In a first step, participants displaying T-values of the FEEL-KJ Total score outside the clinical norm (T-value <40 or >60 in accordance with the transdiagnostic inclusion criterion of substantial emotion dysregulation) and in addition fulfilling the primary diagnosis of either a depressive, anxiety or conduct disorder, will be included in the study. Secondary diagnosis, especially comorbid disorders related to another subgroup of the current trial (e.g., primary diagnosis: depression and secondary diagnosis: anxiety) will be recorded and taken into consideration for the analysis. Age and sex will serve as stratification variables allocating 12 participants of each clinical group to one age block (age block1: 13 + 14 years; age block 2: 15 + 16 years; age block 3: 17 + 18 years) with half of the participants per age block being female and the other half male.

In a second step, a block randomization is performed: 50% of the participants of each block of each subgroup will be randomly allocated to the real or sham tDCS group, respectively (18 of 36 for each of the three clinical groups, female: male = 1:1). This results in 54 subjects per experimental condition (balanced related to clinical groups, age and sex; see Figure 1).

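### The only level given for the three diagnosis tests is an equal split of 0.05; a stated Holm rule would give the same error control with more power when at least two diagnoses respond

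*Protocol article*

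**What the plan says.** The protocol article, under Sample Size Calculations, describes a design with "two treatment conditions (real and sham tDCS), two time points (before and after the intervention) and three diagnostic groups". It takes the level as "0.0167 (0.05 corrected for three groups", with "power 1 – β = 0.80" and "a moderate effect size of f = 0.25". It reports for the primary questionnaire a "test-retest reliability of r = 0.62" and arrives at a "required sample size of 36 per group and 108 subjects overall". Stratification and Randomization allocates patients equally to real and sham stimulation, "18 of 36 for each of the three clinical groups".

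Primary Hypothesis expects the benefit of real stimulation "in total i.e., transdiagnostic, as well as in each clinical subgroup", and Outcomes repeats this for the primary outcome. Statistical Analysis plans a repeated-measures analysis of variance that takes the three clinical subgroups into account, with post-hoc tests for the direction of effects. It gives no significance level and no multiplicity rule for the primary endpoint.

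**The concern.** The article makes one choice about multiplicity for the diagnosis tests: 0.05 divided equally by three. If each test is judged against 0.0167 whatever the other two show, familywise error is controlled, but power is given away. Holm compares the smallest p-value with 0.05/3, the next with 0.05/2 and the last with 0.05, and stops at the first failure. It holds the familywise error at 0.05 under any dependence between the tests, and it rejects everything the equal split rejects and sometimes more.

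This matters because the primary hypothesis is an effect in every diagnosis, and each diagnosis has only 36 patients. Power of 80% for each test separately is well short of 80% for all three together.

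**Working it through.** **Inputs.** From Sample Size Calculations: level 0.05/3 = 0.0167, power 0.80, f = 0.25, two time points, test-retest reliability 0.62. From Stratification and Randomization: 18 real and 18 sham per diagnosis. The article does not say that 0.62 was used as the pre-post correlation; that is inferred from step 1.

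**Step 1: the plan's own figure.** For the time-by-treatment interaction with two arms and two measurements, the F test has 1 and N − 2 degrees of freedom and noncentrality λ = N × f² × 2 / (1 − ρ).

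- N = 36, ρ = 0.62: λ = 36 × 0.0625 × 2 / 0.38 = 11.84. Power at 0.05/3 is 81.6%.
- The smallest even N reaching 80% is 36, and 3 × 36 = 108. The stated size is reproduced.
- Alternatives do not give 36: level 0.05 with ρ = 0.62 needs 26, and level 0.05/3 with ρ = 0.5 needs 46.

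So 0.0167 was applied to each diagnosis separately when the trial was sized. The same noncentrality as a t test on change is √11.84 = 3.44. With 18 per arm this is a standardised difference of 3.44 / √(18/2) = 1.15.

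**Step 2: equal split, equal effect in all three diagnoses.** The diagnoses are separate patients, so the tests are taken as independent.

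- All three significant: 0.816³ = 0.544.
- At least one significant: 1 − (1 − 0.816)³ = 0.994.

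**Step 3: Holm, same data.** Let a, b and c be the power of one test at 0.05/3, 0.025 and 0.05. At N = 36 these are 0.8161, 0.8579 and 0.9166. All three are rejected when all p-values are at most 0.05, at least two are at most 0.025, and at least one is at most 0.05/3:

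P = c³ − (c − b)³ − 3b(c − b)² − (b − a)³ − 3(b − a)²(c − b)

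= 0.7701 − 0.0002 − 0.0089 − 0.0001 − 0.0003 = 0.761 (from unrounded values).

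A simulation of 1,000,000 trials (three independent t tests on change, 34 degrees of freedom) gives the same 76.1%, and 90.0% for power per diagnosis.

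**Step 4: other scenarios** (36 per diagnosis, equal split → Holm).

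| Scenario | Power per truly affected diagnosis | All truly affected diagnoses significant |
|---|---|---|
| Effect in three, ρ = 0.62 | 81.6% → 90.0% | 54.4% → 76.1% |
| Effect in two, ρ = 0.62 | 81.6% → 85.1% | 66.6% → 73.6% |
| Effect in one, ρ = 0.62 | 81.6% → 81.8% | same as per diagnosis |
| 80% of the effect in three, ρ = 0.62 | 59.6% → 69.4% | 21.2% → 42.0% |
| Half the effect in three, ρ = 0.62 | 22.8% → 25.7% | 1.2% → 4.6% |
| Effect in three, ρ = 0.5 | 68.4% → 78.5% | 32.0% → 55.3% |

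The chance of at least one significant diagnosis is the same under both rules in every row, because Holm's first step is the equal-split level. Familywise error with no effect anywhere is 4.9% for both, and Holm's highest value in any simulated scenario is also 4.9%.

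**The case against.** A reader might infer that the plan fixes single-step Bonferroni as its testing rule. The article does not say that. The figure 0.0167 appears once, as an input to the sample size; Statistical Analysis states no level and no rule, and Bonferroni is never named. Sizing at 0.05/3 is also what a cautious statistician would do with Holm in mind. A full analysis plan, not shown, may already name a step-down rule. This stands, and it makes the point conditional: it applies if the stated level is also the testing level.

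Nor can one infer that the sample size is wrong or that error control fails. The equal split is valid, and the plan meets its stated target, 81.6% against 80% per diagnosis. No joint power target for all three diagnoses is set.

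The objection that the gain is selective stands in part. The large figures need a sizeable effect in at least two diagnoses. They also rest on the inferred correlation, and on t tests on change rather than the planned analysis blocked on sex and age.

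Finally, the overall transdiagnostic effect is a primary claim too, and Holm at 0.05 over three diagnoses spends the full 0.05 without covering it. This also stands. It limits what the change achieves, but it does not remove the advantage of stepping down over the three.

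What does not stand is that this is only taste or missing detail. The article states an equal split, and a rule exists that never rejects less at the same error rate.

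**Conclusion.** The point holds as a minor gain in efficiency, not as an error. If 0.0167 is the level at which each diagnosis will be tested, Holm gives the same familywise control. Under the hypothesis the protocol itself states, it adds about 8 points of power per diagnosis and about 22 points for showing the effect in all three. Those figures assume f = 0.25 and a pre-post correlation of 0.62 in every diagnosis, with 18 per arm and no dropout. The gain is about 7 points for both diagnoses if two respond, about 0.2 points if one does, and small in absolute terms at half the assumed effect.

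**What to change.** Keep 108 patients and the 0.0167 sizing level. In Statistical Analysis, before unblinding, state that the three diagnosis tests of the primary endpoint use Holm at familywise 0.05: smallest p-value against 0.0167, next against 0.025, last against 0.05, stopping at the first that fails. If the analysis plan already says so, confirmation is enough.

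State separately where the overall transdiagnostic test stands in the testing order, for example as a gatekeeper before the three or as a fourth member of the family. In the second case the Holm steps change.

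The cost is a few sentences and no patients. The one drawback is that simultaneous confidence intervals matching Holm are less simple than those matching an equal split.

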### Statistical Analysis

Regarding the primary endpoint, repeated-measures analysis of variance (rmANOVA) with Time (pre/post) and Treatment Condition (real stimulation/sham stimulation), as well as considering the three clinical subgroups will be conducted to investigate the interaction between times and groups on the dependent variable [FEEL-KJ raw scores (74)]. The sex and age of the participants will be used as blocking factor accounting for treatment variability between males and females and the three age groups, respectively. In the case of distributions not suitable for conventional testing and missing values, a generalized linear mixed model on the relationship between the stimulation condition and behavioral variables can be applied. Stimulation condition and time will be taken as the fixed-effect factors and the participant's ID as the random-effect factor. Parameters of the model will be fitted with the maximum-pseudolikelihood method, the appropriate distribution and link function according to the characteristics of the response data. A marginal ANOVA will follow to evaluate the fix-effect factors significance. The secondary endpoints, i.e., the indicators for aggression, depression, anxiety and quality of life, as well as cognitive and emotional functioning will be compared using the same approach. In order to identify the direction of effects, *post-hoc* tests will be employed.

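### The effect size labelled moderate (f = 0.25) is a real-versus-sham difference in change of about 1.0 raw-score SD, so 80% power for a moderate effect does not hold within each diagnostic group

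*Protocol article*

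**What the plan says.** All references are to the protocol article. Sample Size Calculations describes a repeated-measures ANOVA with "two treatment conditions (real and sham tDCS), two time points (before and after the intervention") and three diagnostic groups. Its inputs are "α = 0.0167 (0.05 corrected for three groups"), "power 1 – β = 0.80" and "a moderate effect size of f = 0.25". The same paragraph reports that the FEEL-KJ has a "test-retest reliability of r = 0.62". The calculation "results in a required sample size of 36 per group and 108 subjects overall".

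Stratification and Randomization divides each diagnostic group of 36 into 18 real and 18 sham, giving 54 per arm overall. Primary Hypothesis and Outcomes both expect the benefit in the total sample and in each diagnostic subgroup. Statistical Analysis says that the model is used "to investigate the interaction between times and groups on the dependent variable", the FEEL-KJ raw score. Participants gives the recruitment target: "A total of 108 participants". The target difference is nowhere expressed in FEEL-KJ points, and no SD is given.

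**The concern.** The size of effect that a given f represents depends on which effect it describes and how the software scales it. The label moderate for f = 0.25 is familiar from simple between-group comparisons. For the interaction in a 2 x 2 pre-post design, where f is measured against the raw-score SD, the same number stands for a much larger contrast between arms.

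The subgroup comparisons belong to the primary hypothesis, and alpha was divided by three to serve them. A reader who accepts the paragraph will believe that each diagnosis has an 80% chance of showing a moderate benefit. If that chance is nearer one in four, a non-significant result in one diagnosis says little about whether a moderate benefit exists there. With no target in FEEL-KJ points, the reader cannot easily see this.

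**Working it through.** **Inputs.** From the article: alpha = 0.0167, power = 0.80, f = 0.25, 2 arms, 2 time points, 18 per arm within a diagnosis, 54 per arm pooled. Inferred: rho = 0.62 as the pre-post correlation; the article gives it only as retest reliability. Assumed: 0.5 SD as the meaning of moderate. Where a result depends on rho, a range is shown.

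**Step 1: reproduce the 36.** For the interaction with k = 2 arms and m = 2 times, lambda = f² × N × m / (1 − rho), with 1 and N − 2 degrees of freedom.
- N = 36: lambda = 0.0625 × 36 × 2 / 0.38 = 11.84, power 0.816.
- N = 35: power 0.803. N = 34: power 0.788.

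The smallest N is 35, or 36 with equal arms, and 3 × 36 = 108. This matches the article. Other readings at alpha 0.0167 do not: rho = 0.5 gives 45, three groups in the model 43, six groups 57, a between-subjects effect 139, and f defined on the change score 171.

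**Step 2: translate f = 0.25.** Let delta be the difference between arms in pre-post change, in raw-score SDs. In a 2 x 2 interaction each cell mean departs from additivity by delta/4, so f = delta/4 and delta = 4 × 0.25 = 1.0 raw-score SD. The SD of the change score is sqrt(2 × (1 − 0.62)) = 0.872 raw-score SD, so this is 1/0.872 = 1.15 SD of change. A two-sample t test on change scores with 18 per arm and this difference has power 0.816, identical to Step 1.

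**Step 3: power within one diagnosis** (18 versus 18, alpha 0.0167, rho = 0.62). On this scale lambda = (n/2) × delta² / (2 × (1 − rho)) = 9 × delta² / 0.76.

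| delta (raw-score SD) | lambda | power |
|---|---|---|
| 1.0 | 11.84 | 0.82 |
| 0.8 | 7.58 | 0.60 |
| 0.5 | 2.96 | 0.23 |

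The difference detectable with 80% power is 0.98 SD (1.13 at rho = 0.5). For 0.5 SD, power is 0.17 at rho = 0.5, 0.30 at rho = 0.7 and 0.45 at rho = 0.8. Adjusting for baseline instead of analysing change gives 0.29 at rho = 0.62. For scale only: 80% power for 0.5 SD would need 66 per arm, that is 132 per diagnosis and 396 overall.

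**Step 4: pooled comparison** (54 versus 54, 0.5 SD, rho = 0.62). Here lambda = 27 × 0.25 / 0.76 = 8.88. Power is 0.84 at alpha 0.05 and 0.71 at alpha 0.0167.

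**Step 5: withdrawals (secondary).** The required number and the recruitment target are both 108. If withdrawals are not replaced, power per diagnosis for 1.0 SD at rho = 0.62 falls from 0.82 with 36 completers to 0.79 with 34, 0.76 with 32, 0.72 with 30 and 0.68 with 28. These completer numbers are illustrative; the article gives no dropout rate.

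**The case against.** The strongest reply is that nothing was miscalculated. The article claims 80% power for f = 0.25, and its inputs deliver that. The word moderate follows a cited convention, and no FEEL-KJ benchmark in the article says which difference is moderate. The reply is right about the arithmetic. A reader might infer that the sample size is wrong or that 108 fails its own calculation; the article does not support that. The reply does not rescue the label. Under the only reading found to yield 36, the effect is a full raw-score SD between arms, and power at 0.8 SD is 0.60, so the shortfall does not depend on equating moderate with 0.5 SD.

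The use of 0.62 as the correlation is inferred. That stands and has to be disclosed, but no correlation from 0.5 to 0.8 lifts power for 0.5 SD above 0.45.

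A reader might also infer that the whole trial is underpowered. The pooled comparison does not bear that out: it has 0.84 at alpha 0.05 for 0.5 SD. That figure must carry its alpha, because the only level the article states is 0.0167, where power is 0.71.

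Nor does the article say that a non-significant subgroup would be taken as proof of no effect. Its Discussion calls for further research if group differences are not significant. The misreading is a risk, not a stated plan.

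On withdrawals, a replacement rule or inflation may sit in the full protocol, which is not shown, so it cannot be said that dropout was ignored. The mixed model foreseen for missing values would not, however, restore lost sample size.

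**Conclusion.** The concern holds for the diagnostic subgroups. The figure of 36 per diagnosis is internally correct, but it gives 80% power only for a difference of about 1.0 raw-score SD (1.15 SD of change). For 0.5 SD, power is about 0.23, and for 0.8 SD about 0.60. The statement of 80% power for a moderate effect is therefore wrong as worded for the subgroup claims in Primary Hypothesis and Outcomes.

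This rests on two assumptions: that 0.62 served as the pre-post correlation, supported by its reproducing 36, and, for the 0.23 alone, that moderate means 0.5 raw-score SD. The absence of a visible margin for withdrawals is a secondary note, conditional on their not being replaced.

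**What to change.** Keep N = 108 and correct the sample-size paragraph:

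1. Drop the word moderate. State that f = 0.25 for the interaction is a between-arm difference in change of 1.0 raw-score SD, confirm that 0.62 was used as the pre-post correlation, and give the difference in FEEL-KJ points with its SD.
2. State that each diagnostic group has about 80% power only for about 1.0 raw-score SD, and about 23% for 0.5 SD, at alpha 0.0167.
3. State the pooled 54-versus-54 power for 0.5 SD together with its alpha: 0.84 at 0.05, 0.71 at 0.0167.
4. Report subgroup effects with confidence intervals, so that a non-significant subgroup is not read as no effect.
5. Say whether withdrawals are replaced. If they are not, give the power at plausible numbers of completers.

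Items 1 to 5 cost text and a less favourable subgroup power figure; recruitment, randomisation and visits are unchanged. Making the pooled test the sole confirmatory test is optional. It would alter the primary hypothesis and the allocation of alpha, so it is a design decision and not a change of wording.
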